Nevertheless, despite from these clear recommendations, previous studies have found poor adherence to preventive measures (2, 11). In a recent prospective multicenter cohort study from Germany (12), the vaccination status was queried in patients with PSS admitted to an intensive care unit. Only 21% of patients had been vaccinated in the past five years according to the recommendations for asplenic patients with a pneumococcal vaccine; only 6% had ever been vaccinated against meningococci and 12% against *H. influenzae*. Accordingly, only 12% of patients had received a seasonal influenza vaccination. In the asplenia registry study at the Medical Centre University of Freiburg, only 6% of patients treated as part of regular care by general practitioners had completed the vaccination schedule according to current recommendations (13). The registry data also show impressively that the booster immunization rates for each vaccine are again significantly worse than the primary immunization rates. In addition, only a minority (47%) of patients had received prescriptions for stand-by antibiotics.

Reasons for the lack of adherence to recommended prevention measures could be, on the one hand, that the prevention measures are unknown to patients and physicians (8). On the other hand, patients might not be aware of the increased risk of infections, which could explain the low adherence to preventive measures. Several studies suggest the ‘Health Action Process Approach‘ (HAPA) as a theoretical framework for the understanding of health behaviour in general (14-16) and for vaccination behaviour in particular (17-19). The HAPA postulates a two-phase approach to action: Firstly, a pre-intentional motivational phase, which is characterized by risk perception, expectation of action results and expectation of self-efficacy and leads to an intention. And secondly, a post-intentional volition phase, which comprises factors as planning, action control, social support, recovery self-efficacy and leads to the actual health behaviour. Situational barriers and resources also play a role here as they influence the intention, planning and health behaviour. Social support, for example, represents a resource and the lack of it could be a barrier to adopt and maintain health behaviour (20). Interventions to improve health behaviour beyond the passive provision of information material have not yet been described for asplenic patients.

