**Participants and recruitment**

Participants are patients with anatomic asplenia and their physicians (general practitioner or specialists). Eligible are German-speaking patients aged 18 years or older, who are insured by the cooperating health insurance AOK Baden-Württemberg, which is Germany’s 5^th^ largest health insurance and insures more than four million people.

Patient participants are preselected to either the intervention or control group based on the time interval since they underwent splenectomy. Patients who are recently splenectomized (at most 4 months) are allocated to the intervention group. Potential intervention patients are recruited about 6-8 weeks after splenectomy successively by biweekly request from February 2019 for a maximum period of 18 months. The historical control group consists of patients who are splenectomized since more than six months (at most 18 months). Thus, pre-interventional baseline-data on primary and secondary outcomes in the historical control group account for routine care. Potential control group patients were recruited at the start date of study implementation (January 2019) and, to attain the planned sample size, another cohort of patients was contacted half a year later (June 2019).

Potential patient participants are identified via a database search for all splenectomized patients within the predefined group-specific time periods since splenectomy by assistants of the AOK-Baden-Württemberg. Patients who meet criteria receive recruitment letters from the health insurance. Those who are interested in study participation receive detailed information on the procedure, the aims and the legal conditions of the study from the University Medical Centre Freiburg. Participants are asked to provide written informed consent and contact information if they agree to take part. Participants who participate in another clinical intervention trial at the same time are excluded from data analysis.

To identify potential physician participants, participating patients are asked to provide contact information on their general practitioner or other physician who mainly cares for their asplenia and sign an agreement releasing the practitioner form medical confidentially obligation. Physicians whose patients consent to having their physicians included in the study are recruited by letters with information concerning the study. No exclusion criteria for physicians are applied.

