**Sample size considerations**

A priori calculation of the sample size of patient participants to compare the intervention group to the historical control group in the primary outcome was performed with the software ‘*Power and Precision*‘*.* Based on an assumed medium to large effect size of 0.40, a statistical power of 80% and a significance level of 5% (two-sided) the minimum required patient sample of *N* = 100 per group was calculated. Further sample size considerations take into account the actual number of splenectomized patients insured by the AOK. An explorative request showed that 360-400 patients undergo splenectomy a year, resulting in approximately 500 patients assumed to be available for recruitment in the planned inclusion period of 18 months. Based on studies with similar patients (13), we further estimated a proportion of 50% non-respondents for the intervention group and attrition rates of 40% of respondents, so we aim to recruit 500 potential intervention group patients for an expected analysis sample of *N* =178 participants. As this exceeds the statistically required number of cases despite conservative estimations, sufficient cases will be available even after considering potential deceases in the course of the study.

Given that the inclusion period (18 months) is the same for the control group (although retrospectively), sample size considerations for this group are largely the same, with the exception of an assumed proportion of 60% non-respondents and a dropout rate of 50%, resulting in expected *N* = 110 control group cases for analysis. Correspondingly, the number of physician participants included in analysis will be *N* = 178 intervention patients’ physicians and *N* = 110 control patients’ physicians maximum, considering that some patients may have the same physician.

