**Outcome measures**

***Primary outcome***

*The primary outcome*, the adherence to preventative measures, is indicated by a study-specific ‘Preventing PSS-score (PrePSS-score), which includes the following parameters: (1) receipt of guideline-conform pneumococcal and (2) meningococcal vaccinations, (3) prescription and availability of stand-by antibiotics for emergency treatment and (4) handing out of and carrying a medical alert card for asplenic patients. The selection of the included parameters was made by infectious diseases specialists of the University Medical Centre Freiburg based on current prevention recommendations.

To weight these preselected parameters, an expert survey was conducted prior to the study asking a total of sixteen international experts in the care of asplenic patients to rate the items according to their importance in infection prevention, of which nine experts provided feedback. Based on the calculated median of the given expert-ratings the scoring system was defined (see Table 1 for an overview, for exact score formation and operationalization see supplement). The score for each patient is estimated by the study physicians according to both the patient’s and the practitioner’s information gathered through telephone-interviewing. To validate the self-report data on the primary outcome, health insurance patient routine data aggregated by groups (number of vaccinations relevant to asplenia and prescribed emergency antibiotics) will be included.

**Table 1**: Parameters and scoring system of the PrePSS-score

| **Parameter** | **Score range** |
| --- | --- |
| (1) Guideline-conform sequential pneumococcus vaccination | 0-3 |
| (2) Guideline-conform meningococcal vaccination | 0-3 |
| (3) Stand by-antibiotic prescribed and available (‘pill in the pocket‘) | 0-2 |
| (4) Handing-over and carrying a medical alert card | 0-2 |
| **Maximum total PrePSS-score** | **10** |

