**Data analysis**

Demographic characteristics of the study population and effect sizes in the intervention group will be reported descriptively. The main analysis tests the hypothesis that the PrePSS-score at follow-up is higher (better adherence to infection-risk reducing preventive measures) in the intervention group than in the control group. Due to the non-randomized design a propensity score adjustment is performed to reduce potential bias that may be caused by differences on covariates in the two groups (36). We will apply general linear models with propensity score as a covariate. The same method will be used for the analysis of secondary outcomes. Assuming missing data in the questionnaires, multiple imputation will be considered for corresponding analyses. Additional analyses will be conducted with structural equation modeling technique to test a priori specified mediation models of intervention effects.

A cost-effectiveness analysis of the intervention will be conducted by analyzing the change-from-baseline scores of the primary and the secondary outcomes in relation to the costs of the intervention. To reveal the economic efficiency of the intervention, routine data will be used to determine standard treatment and follow-up costs associated with infections requiring hospitalization and with PSS in asplenic patients to contrast them to the intervention costs.

In the qualitative analyses, the audio files of the interviews will be transcribed by an external service provider and the transcripts will be analyzed using a qualitative content analysis.

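### The primary general linear model pools one variance over two unequal groups for a bounded 0-10 score, so its standard error and interval can be modestly wrong; a robust variance would settle this at almost no cost

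*Protocol*

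**What the plan says.** The Data analysis section sets the primary contrast: "The main analysis tests the hypothesis that the PrePSS-score at follow-up is higher" in the intervention group than in the control group. It names the model: "We will apply general linear models with propensity score as a covariate". It mentions no variance estimator, robust standard error or allowance for unequal variances, and it excludes none.

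Three other sections bear on whether one common variance is a good default:

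- **Primary outcome, Table 1.** The score is the sum of four items with ranges 0-3, 0-3, 0-2 and 0-2, so the "Maximum total PrePSS-score" is 10.
- **Sample size considerations.** The calculation requires 100 per group, but 178 intervention patients and 110 controls are expected in the analysis. No standard deviation is given for either group.
- **Background.** Usual-care adherence is low. In the registry, "only 6% of patients treated as part of regular care by general practitioners had completed the vaccination schedule according to current recommendations", and 47% had a stand-by antibiotic prescription. Among intensive-care patients with post-splenectomy sepsis, 21% had recent pneumococcal and 6% had any meningococcal vaccination.

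Under Participants and recruitment, controls are more than 6 and at most 18 months past surgery. Intervention patients are at most 4 months past surgery when allocated, and are scored again after a 6-month follow-up.

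**The concern.** A sum of bounded items has a spread that depends on its mean: small near 0, largest in the middle, small again near 10. The Background figures suggest that controls sit in the lower part of the scale. The study hypothesis is that the intervention group sits higher. The two standard deviations may then differ, and with unequal group sizes a pooled variance no longer gives the right standard error for the difference. If the larger group has the larger spread, the interval is too wide. If it has the smaller spread, the interval is too narrow.

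At stake is the reported precision of the main result. The control group is historical and non-randomised, so the interval around the adjusted difference carries much of the evidence.

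**Working it through.** **1. The plan's own figure.** Per group n = 2(1.960 + 0.842)²/0.40² = 98.1, rounded up to 99; the exact t solution is 99.1. The stated 100 reproduces. At 178 and 110 the expected standardised difference is 0.40 × √(178 × 110/288) = 0.40 × 8.245 = 3.298, so power is Φ(3.298 − 1.96) = 0.91.

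**2. Formula.** With standard deviations s₁ (intervention) and s₀ (control), the pooled standard error divided by the true one is

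r = √{ [((n₁−1)s₁² + (n₀−1)s₀²)/(n₁+n₀−2)] × (1/n₁ + 1/n₀) ÷ (s₁²/n₁ + s₀²/n₀) }.

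Coverage of a nominal 95% interval is 2Φ(1.96 r) − 1. If n₁ = n₀, r = 1 whatever the spreads.

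**3. Inputs.** From the Background: control rates of 6-21% pneumococcal, 6% meningococcal and 47% stand-by antibiotic. Assumed: all-or-none items weighted 3/3/2/2, control alert-card rate 20-50%, latent correlation between items 0-0.5, and all intervention-group rates.

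**4. One case in full.** Independent items.

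- Controls at 6/6/47/20%: variance = 9(0.06)(0.94) × 2 + 4(0.47)(0.53) + 4(0.20)(0.80) = 2.652; SD 1.63.
- Intervention at 50/50/70/70%: variance = 9(0.25) × 2 + 4(0.21) × 2 = 6.18; SD 2.49. The SD ratio is 1.53.
- Pooled variance = (177 × 6.18 + 109 × 2.652)/286 = 4.835. Pooled squared SE = 4.835 × (1/178 + 1/110) = 0.0711. True squared SE = 6.18/178 + 2.652/110 = 0.0588.
- r = √(0.0711/0.0588) = 1.10, so the interval is about 10% too wide and covers about 97%.

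**5. Range over the assumptions, at 178 and 110.**

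| Intervention group | SD ratio | r | Coverage | True effect (SD units) |
|---|---|---|---|---|
| Common shift to the planned effect | 1.08-1.23 | 1.02-1.05 | 95.4-96.0% | 0.40 |
| Mid-scale, 50/50/70/70% | 1.24-1.63 | 1.05-1.11 | 96.1-97.1% | 1.0-1.95 |
| High, 85/85/90/90% | 0.85-1.08 | 0.96-1.02 | 94.1-95.4% | 2.4-4.2 |
| 95% on every item | 0.52-0.68 | 0.87-0.92 | 91.3-92.8% | 3.2-5.6 |

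Scoring the items in grades gave a similar pattern: SD ratio 1.16-1.26 for a small or mid-scale shift, about 1.0 from low to high, and 0.75-0.79 from mid-scale to high.

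**6. Equal means, unequal spreads.** Here the type I error moves. At 178 and 110 the two-sided size is 6.2% for an SD ratio of 0.8, 4.9% for 1.0, 3.8% for 1.25 and 3.1% for 1.5. With an estimated propensity score as covariate, simulated rejection over ratios 0.67-1.5 was 3.4-6.9% with ordinary standard errors and 5.1-6.0% with HC3 (Monte Carlo standard error about 0.5 points).

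**7. Group sizes.** The stated response and dropout rates give 500 × 0.5 × 0.6 = 150 and 500 × 0.4 × 0.5 = 100, not 178 and 110. At 150 and 100 the pattern is the same and slightly weaker: a ratio of 0.8 gives size 6.0%, and 1.5 gives 3.3%.

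**The case against.** The strongest objection is that a protocol may name a model family and leave the variance estimator to the statistical analysis plan, which is not at hand. Nothing in the Data analysis section rules out a robust standard error. That stands: this is a refinement of a choice the protocol has made, not an error or contradiction in it.

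Second, the inputs are weak. The 21% and 6% vaccination figures come from intensive-care patients with sepsis, not from the control population. Exact item scoring is in a supplement that is not shown, and every intervention rate is assumed. That also stands, and it is why only ranges are given.

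Third, the imbalance is not certain. The Discussion speaks of propensity score matching. If that meant 1:1 matching, the groups would be equal and the problem would largely disappear.

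Stronger readings are tempting, but the documents do not support them:

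- A reader might infer that the test **is** miscalibrated. It is so only if the spreads differ and the groups are unequal. In some large-effect scenarios the SD ratio is about 1.
- A reader might infer an inflated false-positive rate from the near-ceiling scenarios. Those contain a large real effect. If the spreads differ only because the intervention works, the two distributions are equal under no effect and the test keeps its level.
- A reader might infer a marked loss from the planned 80% power. At 178 and 110 power is about 91%. A standard error 2-5% too large lowers it to about 90-89%: Φ(3.298 − 1.96 × 1.02) = 0.903 and Φ(3.298 − 1.96 × 1.05) = 0.893.
- A reader might extend the point to the secondary scales, for which the same method is planned. The documents give no rates or spreads for them that would support this.

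**Conclusion.** The point holds as a conditional one of low severity. A standard general linear model on this bounded score, with 178 and 110 patients, can misstate the standard error and interval if the group spreads differ.

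Near the planned effect the error is small and conservative. It reaches about 11% too large at mid-scale, and 3-4% too small or worse only near the ceiling. The large errors, in either direction, need true effects of about one standard deviation or more. The test's conclusion would not change there; only the interval width would. These sizes rest on the assumed item rates and all-or-none scoring.

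The type I error is at issue only if the spreads differ without a mean effect. Controls are scored over a 12-month range of time since surgery, and the intervention group probably over a narrower one. This makes such a difference possible, but the documents do not quantify it.

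**What to change.** In the Data analysis section, for the primary PrePSS-score comparison, add that the general linear model with group and propensity score will use heteroscedasticity-consistent (HC3) standard errors or, alternatively, group-specific residual variances. Name one of the two before the data are seen.

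HC3 leaves the effect estimate as it is and changes only its standard error, interval and p-value. The cost is one sentence and one software option. If the variances prove equal, the loss of efficiency is negligible at these group sizes.

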**Methods**

**Aims and hypotheses**

The purpose of this study is to develop, manualize and evaluate a novel intervention that educates both patients and their physicians on appropriate preventive measures that should be undertaken to prevent infections after splenectomy. Besides information provision, the intervention is intended to motivate patients to implement the preventive measures and to convey action-related skills such as planning and managing barriers. It will be evaluated whether this targeted intervention (intervention group) is superior to usual care (historical control group) in terms of primary and secondary study outcomes. More precisely, we have put forward the following hypotheses as to the outcome of the intervention: (a) Adherence to infection-risk reducing preventive measures will significantly be increased (primary outcome). As a result, (b) the incidence of severe infections associated with asplenia (particular PSS) and (c) related health-care costs covered by health insurances will be reduced (distal secondary outcomes). (d) Risk perception, intention to implementation, perceived self-efficacy, action and coping-planning, positive and negative outcome expectations and received social support (HAPA-related variables) expected to account for the effect of the intervention will significantly be enhanced (proximal secondary outcomes). Furthermore, (e) disease knowledge, patients’ general and asplenia-specific self-management, asplenia-specific health literacy, patient involvement as well as health-related quality of life will significantly be enhanced (distal secondary outcomes).

Beside this quantitative outcome-evaluation, intervention patients’ and intervention patients’ physicians’ acceptance and evaluation of the intervention will be inquired in telephone interviews in a process-evaluating part of the study.

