***Secondary outcomes***

In this article secondary patient outcomes are classified on a proximal-distal continuum of outcome measures (25). HAPA-related variables (i.e. patient’s risk perception, self-efficacy and action-planning) are considered as *proximal secondary outcomes* which are assumed to be more likely and directly affected by the intervention than distal outcomes and observable shortly after the intervention. More global, *distal secondary outcomes,* are assumed to be also influenced by proximal outcomes as well as external, non-treatment factors. These include disease knowledge (disease knowledge is also expected to be a confounder), patient general and asplenia-specific self-management as well as asplenia-specific health literacy, self-reported patient involvement and health-related quality of life.

*Secondary outcomes for physician participants* are their subjective improvement in knowledge and their satisfaction with the intervention.

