Six items measuring *behavioral intention* to obtain prevention refer, for instance, to “undertake preventive measures recommended after splenectomy” and “obtain vaccinations”. *Perceived self-efficacy* is assessed by ten items asking participants to rate their level of confidence in their ability to implement and cope with preventive measures, such as “I can correctly interpret symptoms of a severe infection” or “I will renew my emergency antibiotics after the expiration date”. *Prevention behavior* *planning* is assessed with six items, four items measuring action planning as the items address the where and how of the precautions (e.g. “what kind of vaccinations I will get done”) and two items measuring coping planning asking for situations that could interfere with their plans (e.g. “what I can do if I forget my emergency antibiotics”). *Positive and negative outcome expectancies* after implementing the preventive measures are assessed with three items asking for pros, e.g. “I’m better protected from the flu” and three items asking for cons, e.g. “I could suffer from side effects of vaccinations”. *Received social support* regarding prevention implementation is measured with the stem “People around me (e.g. family, friends)…” followed by five items, for example “have encouraged me to take preventive measures recommended after splenectomy”. For *risk perception*, the item stem “If I compare myself with other people (of my age and sex), then my risk, sometime in future…” is followed by the items “to fall ill with blood poisoning”, “to fall ill with meningitis” and “to get pneumonia”, which are rated by participants on a scale from *significantly increased* (1) to *considerably lower* (5).

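### For hypothesis (d), the only post-call group comparison of HAPA scores cannot be separated from time since surgery, and no inferential test of the intervention group's own t0-t1 pair is stated

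*Protocol*

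**What the plan says.** Aims and hypotheses asks whether the intervention "is superior to usual care (historical control group) in terms of primary and secondary study outcomes". Hypothesis (d) concerns the HAPA variables (risk perception, intention, self-efficacy, planning, outcome expectations, social support), which are "expected to account for the effect of the intervention will significantly be enhanced (proximal secondary outcomes"). Under Secondary outcomes they are described as "observable shortly after the intervention".

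Data analysis gives the model for the primary comparison: "We will apply general linear models with propensity score as a covariate". It then extends this to the rest: "The same method will be used for the analysis of secondary outcomes".

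The groups are defined by time since surgery (Participants and recruitment): "Patients who are recently splenectomized (at most 4 months) are allocated to the intervention group"; "The historical control group consists of patients who are splenectomized since more than six months (at most 18 months").

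Under Procedure, intervention patients complete the HAPA items before the call (t0) and, in similar form, after it (t1). The six-month questionnaire (t2) covers distal outcomes only. Controls are measured at t0 and not again.

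**The concern.** The group model suits an outcome measured at t2 better than one measured at t1. By t2, intervention patients have moved into the time range after surgery that the controls occupy. Applied to HAPA scores, the same model compares people early after surgery who have just finished a motivational call with people at least half a year out who have had no call. Two things differ at once, and the analysis cannot tell them apart.

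Time since surgery could plausibly matter for these scales. Some items look forward, such as the planning item "what kind of vaccinations I will get done", and a patient already vaccinated may answer them differently from one who is not. Others, such as support received from family and friends, look back and may rise with time.

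At stake is the inference on mechanism. The HAPA variables are meant to explain the intervention effect, and mediation models are planned. A group difference that reflects time since surgery could be read as evidence that the call worked through intention or planning.

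**Working it through.** **1. Which contrast the plan implies.** HAPA measurements available under Procedure:

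| Group | t0 | t1 | t2 |
| --- | --- | --- | --- |
| Intervention | yes | yes | no |
| Control | yes | no | no |

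A group comparison after the call can only be intervention t1 against control t0. The intervention group's t0 score cannot enter as an ordinary baseline covariate, because the controls' t0 score is their outcome.

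**2. Overlap in time since surgery.** The entry windows are at most 4 months (intervention) and more than 6 to 18 months (control). They are disjoint, so time since surgery at entry determines group membership completely. Neither covariate adjustment (Data analysis) nor the matching mentioned in the Discussion can balance it.

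For comparison, t2 follows six months after the call. If the call came at about 6-8 weeks, t2 falls at about 7.5-8 months; if it came at 4 months, t2 falls at 4 + 6 = 10 months. Both lie inside the control window, so the problem is specific to t1.

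**3. The plan's own figure.** Sample size considerations gives 100 per group for effect size 0.40, 80% power and two-sided 5%. The normal approximation gives 99 and the two-sample t-test 99.08, rounded up to 100, so the figure reproduces. It applies to the primary outcome; none is given for (d).

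**4. Patient numbers used.** From the stated base and loss rates: 500 × 0.5 × 0.6 = 150 intervention and 500 × 0.4 × 0.5 = 100 control. The protocol prints 178 and 110; results for both follow.

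**5. Rejection rate with no effect of the call.** In SD units, SE = √(1/150 + 1/100) = 0.129 (178 and 110: 0.121). For a residual shift b due to time since surgery alone, the two-sided 5% test rejects with probability Φ(b/SE − 1.96) + Φ(−b/SE − 1.96). The values of b are assumptions.

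| Assumed b (SD) | 150 vs 100 | 178 vs 110 |
| --- | --- | --- |
| 0.1 | 12% | 13% |
| 0.2 | 34% | 38% |
| 0.3 | 64% | 70% |

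**6. Precision of the paired contrast.** SE = √(2(1 − r)/150), with the t0-t1 correlation r assumed and equal SDs.

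| Assumed r | Paired SE (SD) | Between-group SE ÷ paired SE |
| --- | --- | --- |
| 0 | 0.115 | 1.12 |
| 0.3 | 0.097 | 1.34 |
| 0.5 | 0.082 | 1.58 |

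Precision is secondary: the group comparison has 87% power for 0.40 SD at 150 vs 100, and 91% at 178 vs 110.

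**The case against.** The comparison with usual care is deliberate, and a before-after contrast taken straight after a motivational call has weaknesses of its own: no concurrent control, possible immediate-response effects, and t1 items that are only similar to those at t0. This stands, and it is why the limits of the paired contrast must be stated. But t1 against control t0 uses the same t1 scores and has the same immediate-response weakness, with confounding by time since surgery added.

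The protocol does not name the time point for (d). That it is t1 against control t0 follows from the schedule, and a statistical analysis plan, not at hand, may spell it out. The model itself, however, is already fixed in the protocol.

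Several stronger readings are tempting but not supported:

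- *That the t0-t1 pair is discarded.* It can feed the descriptive effect sizes in the intervention group and the change scores in the cost-effectiveness analysis. Only an inferential test of it is absent.
- *That the bias favours the intervention.* A control past the planning stage might score low on intention, but backward-looking support items could run the other way, and risk perception need not fall with vaccination. The Background also reports that only 6% of patients in regular care had completed the vaccination schedule and 47% had stand-by antibiotics, so few controls may be past that stage.
- *That t1 falls within a known number of months after surgery.* Four months is a limit at allocation; no maximum interval to the call is given.
- *That 34% or 64% is the expected error rate.* Both follow from assumed shifts for which the protocol offers no data.

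**Conclusion.** The point holds for hypothesis (d). Under the stated model and schedule, the only post-call group test of the HAPA variables is confounded with time since surgery by construction, and no propensity method can remove this. A significant difference, or its absence, could not be attributed to the call. The protocol states no inferential test of the pair that measures change across the call in the same patients.

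The size depends on an unknown residual shift: rejection is 12% at 0.1 SD, 34% at 0.2 and 64% at 0.3 with 150 and 100 patients, against a nominal 5%. The direction may differ by construct. The reason to change is attribution; the gain in precision, 1.12 to 1.58 times for assumed correlations of 0 to 0.5, is a side benefit. The point concerns one family of secondary outcomes and does not touch the primary comparison at t2.

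**What to change.** In Data analysis, limit the sentence on secondary outcomes to those measured at t2 and keep the propensity-adjusted model for them. For hypothesis (d), add a paragraph stating that:

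- the inferential test is the paired change from t0 to t1 in the intervention group, reported as mean change with 95% CI;
- this is a short-interval before-after contrast without a concurrent control and may include immediate-response effects;
- intervention t1 against control t0 is a supportive analysis only, labelled as not separable from time since surgery, and no claim of superiority over usual care on HAPA variables rests on it.

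The wording of (d) under Aims and hypotheses should be aligned with this. The cost is one paragraph of text and no new data. The downside is a weaker claim: change from before to after the call instead of superiority to usual care.
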